## 6.11 Secondary Outcome Measure

The secondary outcome measures are accommodative amplitude and response, pupil size, other ocular biometrics, which will be collected during first-, sixth-, twelfth- and 18^th^-month visits. Treatment compliance is checked by self-reporting log by participant at all the time points. Instillation of eye drop is checked by self-reporting log at all the time points. Information regarding to any adverse events or intervention events and whether they are related to the active treatment will be collected at all the time points.

All other measurements will be classified as exploratory outcomes.

## 6.12 Schedule of Intervention and Follow-up

| Procedures | Screening Questionnaire | Visit 0-1: Eligibility / Baseline | Visit 2: Spectacles and  Eye Drop Dispensing | Visit 3: First Month Aftercare | Visit 4-5: Sixth- and Twelfth-Month Follow-up | Visit 6: 18-Month Follow-up |
| --- | --- | --- | --- | --- | --- | --- |
| Informed Consent |  | X |  |  |  |  |
| Demographics | X | X |  |  |  |  |
| Medical History | X | X | X | X | X | X |
| Parental and Subject Refractive Status Questionnaire | X | X |  |  |  |  |
| Randomization |  | X |  |  |  |  |
| Administer Study Intervention |  |  | X | X | X |  |
| Visual Acuity (Habitual; D&N) |  | X | X | X | X | X |
| Cover Test |  | X |  |  | X | X |
| Interpupillary Distance |  | X |  |  | X | X |
| Non-cycloplegic Autorefraction and Keratometry |  | X |  |  | X | X |
| Non-cycloplegic Subjective Refraction and BCVA |  | X |  |  | X | X |
| Phoria |  | X |  |  | X | X |
| Anterior Ocular Health |  | X | X | X | X | X |
| NCIOP |  | X | X | X | X | X |
| Pupil Size |  | X | X | X | X | X |
| Stereopsis |  | X |  |  | X | X |
| Amplitude of Accommodation |  | X | X | X | X | X |
| Accommodative Lag |  | X |  |  | X | X |
| Contrast Sensitivity |  | X |  |  | X | X |
| Optical Coherence Tomography |  | X |  |  | X | X |
| Procedures | Screening Questionnaire | Visit 0-1: Eligibility / Baseline | Visit 2: Spectacles and  Eye Drop Dispensing | Visit 3: First Month Aftercare | Visit 4-5: Sixth- and Twelfth-Month Follow-up | Visit 6: 18-Month Follow-up |
| Cycloplegia |  | X |  |  | X | X |
| Cycloplegic Autorefraction |  | X |  |  | X | X |
| Peripheral Refraction |  | X |  |  | X | X |
| Cycloplegic Subjective Refraction |  | X |  |  | X | X |
| Axial Length |  | X |  |  | X | X |
| Ocular Biometry |  | X |  |  | X | X |
| Dilated Fundus Ophthalmoscopy |  | X |  |  | X | X |
| Order Spectacle Lenses |  | X |  |  | X | X |
| Verification of Spectacle Lenses |  |  | X | X | X | X |
| Verification of Atropine |  |  | X | X | X | X |
| Spectacle Lenses Dispensing |  |  | X |  | X | X |
| Atropine Dispensing |  |  | X | X | X | X |
| Visual Performance Questionnaire |  |  |  | X | X | X |
| Spectacle Wear and Eye Drop Log |  |  | X | X | X | X |
| Adverse Event Review and Evaluation | X | X | X | X | X | X |
| Complete Case Report Forms (CRFs) | X | X | X | X | X | X |

*Abbreviations: D&N Distance and Near; BCVA Best Corrected Visual Acuity; IOP Intraocular Pressure*

## 6.13 Data Collection Schedules

The following steps will be conducted by study personnel:

### 6.13.1 Eligibility, baseline assessments and randomization

- Screen potential participants through screening questionnaire and acquire contact details.
- Screen eligible participants through eligibility assessment (Case Report Form (CRF) in Research Electronic Data Capture (REDCap)).
- Perform baseline assessment on participants for eligibility (CRF Baseline in REDCap).
- Record refractive history (CRF RxHx in REDCap).
- Randomization of participants via REDCap (Randomization Log in REDCap).

### 6.13.2 Spectacles and atropine dispensing

- Order the type of spectacle lenses (Single vision or DIMS lenses) according to randomization (Randomization Log in REDCap) by an unmasked investigator.
- Order, record and dispense type of eye drops (atropine 0.01%) by an unmasked investigator (data recorded in CRF eyedrop in REDCap)
- Record results of delivery visual assessments (CRF Delivery in REDCap).

### 6.13.3 Follow-up assessments (data related to treatment outcomes)

The following steps will be completed by study personnel at the first-, sixth-, twelfth-, and 18-month follow-up appointments:

- Record results of follow-up visual assessments (CRF FU in REDCap).
- Record treatment compliance data (Treatment Compliance Log in REDCap).
- Record visual performance and treatment acceptability outcome data (Spectacle Vision and Comfort Questionnaire in REDCap).
- Record any adverse events affecting the participant and any incidental events (CRF AE in REDCap).
- Update spectacle lenses if required (CRF Delivery in REDCap).

## 6.14 Protocol Violations

A deviation from the protocol when no amendment has been submitted and approved would be regarded as a protocol violation. All protocol violations must be documented and reported (CRF V in REDCap). Prescribed treatment dose of spectacles is at least 70 hours each week (10 hours of spectacle wear per day, 7 days a week) and treatment dose of eye drop is two drops of eye drop every day, seven days a week. A participant is considered as compliant to the study protocol if he or she has worn the spectacle for at least 56 hours a week (7 days of at least 8 hours). If the spectacle lenses are worn for less than 35 hours per week, or eye drops are put on for less than three days per week, it is defined as a protocol violation. A list of such patients will be prepared prior to unblinding.

# 7. Statistical Considerations

## 7.1 Sample Size

In the study regarding low dose atropine for myopia control, mean change in refractive error after one year was 0.64 ± 0.56D (mean ± SD) (10). Our previous randomized clinical trial showed DIMS slowed down myopia progression by approximately 60% (8). The sample size is calculated based on an assumption that, adopting atropine and DIMS together will result in a 60% reduction of mean refractive error change relative to using only atropine, the difference detected between two groups (atropine alone vs. atropine and DIMS) will be 0.384 (0.64 x 60% = 0.384), and the effect size will be 0.685 (0.384/0.56 = 0.685). According to power analysis (G*Power Version 3.1.9.2), 46 subjects are required per group to achieve 90% power with a significance level of 0.05 (two-tailed). Assuming the dropout rate will be 20%, 56 subjects will be required for each group in this proposal. Therefore, 112 subjects (56 subjects × 2 groups) will be required for the entire study.

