**Statistical Methods**

*Sample Size Calculation*

In the study regarding low dose atropine for myopia control, mean change in refractive error after one year was 0.64 ± 0.56D (mean ± SD) (10). Our previous randomized clinical trial showed DIMS slowed down myopia progression by approximately 60% (8). The sample size is calculated based on an assumption that, adopting atropine and DIMS together will result in a 60% reduction of mean refractive error change relative to using only atropine, the difference detected between two groups (atropine alone vs. atropine and DIMS) will be 0.384 (0.64 x 60% = 0.384), and the effect size will be 0.685 (0.384/0.56 = 0.685). According to power analysis (G*Power Version 3.1.9.2), 46 subjects are required per group to achieve 90% power with a significance level of 0.05 (two-tailed). Assuming the dropout rate will be 20%, 56 subjects will be required for each group in this proposal. Therefore, 112 subjects (56 subjects × 2 groups) will be required for the entire study.

As the quantitative effectiveness of DIMS combined with atropine is not known, two conservative assumptions are made during the sample size calculation: standard deviations are the same in the atropine plus DIMS group relative to the atropine alone group; and the previous study considering atropine tracked a 12-month change, while the proposed study treatment period will be 18 months.

*Statistical Analysis*

Data of right eyes will be used for analyses. Demographic and optometric data will be displayed as mean and standard deviation, or number and percentage as appropriate. The Chi-square test (or if appropriate Fisher’s Exact test) and unpaired t-test will be performed to compare baseline between-group differences in demographics (age, sex) and primary and secondary outcomes between the control group. Myopia progression over 18 months will be calculated as the difference between the primary outcomes (SER and AL) at the sixth and the first visits.

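### The 20% dropout allowance is slightly short: 56 per group leaves about 45 completers, not the 46 the plan requires (minor)

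*Combined protocol and SAP*

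**What the plan says.** Section 7.1 (Sample Size) and the Statistical Methods part of the Overview give the same calculation. They take a one-year mean change on low-dose atropine of 0.64 D with SD 0.56 D, assume a 60% reduction from adding DIMS lenses, and so plan for a difference of 0.384 D and a standardised effect of 0.685. The Overview adds that "standard deviations are the same in the atropine plus DIMS group relative to the atropine alone group". From this the plan concludes, using G*Power and a two-sided 5% level, that "46 subjects are required per group to achieve 90% power".

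The dropout step follows at once: "Assuming the dropout rate will be 20%, 56 subjects will be required for each group in this proposal". Doubling gives the total of 112. No formula is shown for going from 46 to 56.

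**The concern.** A dropout allowance should leave the required number after the expected losses. Here the paragraph gives the required number (46), the expected loss (20%) and the number to enrol (56), and 80% of 56 is not 46. The result is what one gets by adding 20% to 46 instead of dividing 46 by the 80% who remain, a common slip.

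At stake is whether the stated 90% power holds under the plan's own dropout assumption. The figures appear in two places, and the Overview says that CONSORT will guide reporting, so they are likely to be carried into the trial report.

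**Working it through.** **Inputs, all from section 7.1 and the Overview:** difference 0.384 D; SD 0.56 D in each group; two-sided α = 0.05; target power 90%; 46 per group before dropout; dropout 20%; 56 per group and 112 in total. Allocation is 1:1 (section 6.5) and the primary test is an unpaired t-test (section 7.2.2).

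**Step 1: reproduce 46.** The effect size is d = 0.384/0.56 = 0.6857 (printed as 0.685). For a two-sample t-test with n per group, power comes from the noncentral t distribution with 2n − 2 degrees of freedom and noncentrality d√(n/2).

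| n per group | Power |
| --- | --- |
| 44 | 88.9% |
| 44.8 | 89.4% |
| 45 | 89.6% |
| 46 | 90.2% |

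The smallest whole number reaching 90% is 46, as stated. Using d = 0.685 changes these powers by less than 0.1 point.

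**Step 2: the dropout step.**
- Multiplying: 46 × 1.2 = 55.2, rounded up to 56. This matches the plan.
- Dividing: 46/(1 − 0.20) = 57.5, rounded up to 58 per group, or 116 in total.
- Difference: 2 per group, 4 in total (4/112 = 3.6%).

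**Step 3: what 56 delivers.**
- Expected completers at 20% dropout: 56 × 0.8 = 44.8 per group. For comparison, 58 × 0.8 = 46.4.
- Power at 44.8 per group: 89.4%. Over 44 to 45 completers it is 88.9% to 89.6%, so the shortfall against 90% is 0.4 to 1.1 points.
- Largest dropout that still leaves 46: 1 − 46/56 = 17.9%, which is 10 losses per group.

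**The case against.** **The size is negligible.** This stands. With 44.8 per group, 90% power returns if the true difference is 0.388 D instead of 0.384 D. A change of 0.004 D is far finer than the planning inputs, which rest on a reduction the plan itself calls approximate. The Overview also describes its use of a 12-month change for an 18-month trial as conservative.

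**The multiplier of 1.2 is inferred.** This stands too. The normal approximation gives an unrounded n of about 44.7, and 44.7/0.8 = 55.9 also rounds up to 56. But the plan starts from 46 by G*Power, not from 44.7. The mismatch between 46, 20% and 56 does not depend on how 56 was reached.

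**Dropouts are not simply lost.** Section 7.2.4 makes intention-to-treat with multiple imputation the main analysis, so completer power describes the complete-case sensitivity analysis most directly. The 6- and 12-month measurements in section 6.12 would inform the imputation for later dropouts. Section 6.7 also allows some very early losses to be replaced. These points soften the effect but do not reconcile the figures. Imputation recovers only part of the lost information, and section 7.1 takes no credit for it. Replacement covers only participants who never received the intervention, or who left within two weeks because they could not meet the inclusion criteria while recruitment was open. Section 6.7 also ends scheduled data collection when treatment stops, so later losses will generally lack an 18-month outcome.

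**Stronger readings that the documents do not support.**
- A reader might round down to 44 completers and quote 88.9%. The expected number is 44.8, which is nearer 45.
- A reader might add a further loss of power from having to succeed on both refraction and axial length. The plan names two primary outcomes but nowhere says that both must succeed.
- A reader might expect covariate adjustment to make up the shortfall. Section 7.2.2 uses analysis of covariance only if baseline demographics differ significantly, and the plan gives no covariate–outcome correlation from which to compute a gain.

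**Conclusion.** The point holds as a minor arithmetic inconsistency. Significance level, effect size, 46 per group and 90% power agree with one another; only the final inflation to 56 falls short, by 2 per group. At the plan's own 20% dropout the completer-based power is about 89.4%, roughly half a point below the stated 90%.

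This rests on the plan's effect size and common SD, equal dropout in the two groups, and dropouts contributing no 18-month data. To the extent that imputation recovers information, the shortfall is smaller still. A reader might infer that the trial is materially underpowered; a loss of 0.4 to 1.1 points does not support that.

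**What to change.** Keep enrolment at 112 and correct the statement in section 7.1 and in the Overview. Suggested wording: *56 per group retains 46 completers at up to 17.9% dropout; at 20% dropout about 45 per group remain, with just over 89% power.* This costs one sentence in two places and changes no procedure or analysis.

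If the sponsor prefers to keep both the 20% allowance and the 90% claim, the matching figure is 58 per group, 116 in total, at the cost of four more children. The size of the shortfall does not demand this.

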## 7.2 Statistical analysis

Statistical analyses will be performed using SPSS. Data of right eyes will be used for analyses. Data from the trial will be entered into an excel spreadsheet and extracted into a statistical program for analysis. Data analyses will be specified *a priori* in a statistical analysis plan (SAP) prepared by the researchers (and agreed upon by all members of the Steering Committee). All statistical tests will be two-tailed and a 5% significance level maintained throughout the analyses.

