**Criteria for Evaluation**

*Primary outcomes*

The primary outcome measures are changes in cycloplegic refraction in spherical equivalent and axial length over 18 months from baseline.

*Secondary outcomes*

The secondary outcome measures are accommodative amplitude and response, pupil size, other ocular biometrics, treatment compliance, and adverse events and intervention events at all visits.

Other optometric outcomes not listed here will be considered exploratory in nature.

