Unpaired t-test will be used to compare the changes in primary outcomes between two groups. If statistically significant differences in baseline demographic characteristics between groups are found, these significant covariates will also be adjusted in these primary analyses with Analysis of Covariates. In this case, both the unadjusted and adjusted results will be reported. Multiple regression analysis with the primary outcomes at the sixth visit will act as the dependent variable and independent variables, alongside with the secondary outcomes, will be employed to identify factors that may associated with myopia control effectiveness.

All analyses will use intention-to-treat analyses. Missing values of outcome variables and covariates will be replaced using multiple imputation procedure with 10 sets of imputations assuming missing at random. Sensitivity analyses for the primary outcomes include complete case analysis and per-protocol analysis. All analyses will be 2-tailed with a significance level of 5%.

The CONSORT Statement will guide the reporting of results.

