### 7.2.2 Treatment effects

The effectiveness of myopic control will be calculated as:

1 – (progression therapy) / (progression control)

Unpaired t-test will be used to compare the changes in primary outcomes between two groups. If statistically significant differences in baseline demographic characteristics between groups are found, these significant covariates will also be adjusted in these primary analyses with Analysis of Covariates. In this case, both the unadjusted and adjusted results will be reported. Multiple regression analysis with the primary outcomes at the final visit will act as the dependent variable and independent variables, alongside with the secondary outcomes, will be employed to identify factors that may associate with myopia control effectiveness.

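### Two unranked primary outcomes are each tested at 5% with no rule for declaring success, and the 90% power covers refraction only

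*Combined protocol and SAP*

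**What the plan says.** The Overview (Criteria for Evaluation) states: "The primary outcome measures are changes in cycloplegic refraction in spherical equivalent and axial length over 18 months from baseline". Section 6.10 repeats this with the instruments, and the registration data set in section 2 also lists both outcomes. None of the three ranks them.

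Section 7.2.2 gives the primary test: "Unpaired t-test will be used to compare the changes in primary outcomes between two groups". Section 7.2 sets the level: "All statistical tests will be two-tailed and a 5% significance level maintained throughout the analyses". The Overview's Statistical Methods says the same. There is no order of testing, no division of the 5%, and no statement that both must succeed. Section 7.2.5 plans no interim efficacy analysis, so the two outcomes are the only source of primary multiplicity considered here.

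The sample size in section 7.1 rests on refraction alone. It assumes a "60% reduction of mean refractive error change relative to using only atropine" and concludes that "46 subjects are required per group to achieve 90% power with a significance level of 0.05 (two-tailed)". No expected difference, standard deviation or power is given for AL.

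**The concern.** Section 6 describes a superiority trial, and section 9.5 accepts that it is meant to give definitive information on effectiveness and/or safety. Such a trial should say in advance which result counts as success. Here two readings are open.

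- Either outcome suffices. Two chances at 5% then give an overall false-positive probability above 5%.
- Both are required. The false-positive probability stays at or below 5%, but the trial must win twice, and the power calculation covers only one of the wins.

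If the rule stays open until results are known, it can be settled by whichever outcome reached p < 0.05. No later analysis can credibly repair that.

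**Working it through.** **Inputs from section 7.1.** Control change 0.64 D, SD 0.56 D, 60% reduction, two-sided 0.05, 46 evaluable per group. **Not in the documents, so assumed:** the correlation ρ between the two test statistics, and the standardised effect d on AL. Under the null, the two-sided error depends only on the size of ρ. For power, ρ is taken with both outcomes coded in the direction of benefit.

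**1. The plan's own figure.** Difference = 0.64 × 0.60 = 0.384 D, and d = 0.384/0.56 = 0.686 (printed as 0.685). For a two-sample t-test with n = 46 per group, the degrees of freedom are 2 × 46 − 2 = 90 and the noncentrality is d√(n/2) = 0.686 × √23 = 3.29. The noncentral t distribution gives power 90.2%; at n = 45 it is 89.6%. So 46 per group for 90% is reproduced, for refraction.

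**2. Either outcome suffices.** With neither outcome affected, the family-wise error is 1 − P(|Z₁| ≤ 1.96 and |Z₂| ≤ 1.96), with (Z₁, Z₂) bivariate normal with correlation ρ. At ρ = 0 this is 1 − 0.95² = 9.75%.

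| ρ (assumed) | 0 | 0.6 | 0.7 | 0.8 | 0.9 | 0.95 |
|---|---|---|---|---|---|---|
| Family-wise error | 9.75% | 8.8% | 8.4% | 7.8% | 7.0% | 6.5% |

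It is above 5% at every correlation below 1.

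**3. Both outcomes required.** A false claim needs at least one true null to be rejected at 5%, so the error is at most 5%. Joint power is Φ₂(m₁, m₂; ρ), the bivariate normal distribution function with each m set to Φ⁻¹ of that outcome's noncentral-t power at 46 per group. For SER, m₁ = Φ⁻¹(0.902).

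| AL effect d (assumed) | AL power alone | Joint power, ρ from 0.6 to 0.9 |
|---|---|---|
| 0.5 | 66% | 64% to 66% |
| 0.6 | 81% | 77% to 80% |
| 0.686 (same as SER) | 90% | 84% to 87% |
| 0.8 | 97% | 89% to 90% |

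Joint power cannot exceed the smaller of the two separate powers, so on the plan's SER assumptions it is at most 90.2% whatever AL does. Within these ranges the AL effect matters far more than the correlation.

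**The case against.** Four points can be made for the plan.

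*The 5% is kept.* A reader might infer that the plan promises a 5% overall error rate and breaks it. The text does not support that. The wording in section 7.2 and the Overview reads as a level for each test, and each test meets it. Family-wise error is not mentioned. What stands is that nothing controls it if either outcome may carry the claim.

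*The 90% is right.* A reader might infer that the stated power is wrong. It is not: section 7.1 ties it to refractive error change, where it reproduces. The plan claims no joint power. What stands is that AL power and joint power are missing.

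*SER and AL are closely related.* Positive correlation is plausible, although the documents give no figure. It shrinks the inflation, but 6.5% remains at ρ = 0.95, and correlation does not supply a success rule.

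*A SAP will settle it.* Section 7.2 says analyses will be specified a priori in a SAP agreed by the Steering Committee, and section 2 labels the trial phase 2. Both limit the weight of the omission. But the supplied text contains no such rule, and the success criterion belongs with the definition of the primary outcomes.

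**Conclusion.** The point holds as a missing decision rule and a missing power basis for AL. Silence leaves the rule undefined; it does not amount to an either-or rule, so the inflation is conditional. If either outcome may support superiority, family-wise error is 9.75% under independence and 8.8% to 7.0% for correlations of 0.6 to 0.9. If both must, error is controlled and joint power is unstated: about 84% to 87% if AL has the same standardised effect as SER, but 64% to 66% at d = 0.5 and 89% to 90% at d = 0.8. All of these rest on assumed correlations, and the power figures also on assumed AL effects. The documents cannot narrow them.

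This should be fixed. Treatment, conduct and the SER sample size are unaffected, and a short statement made before outcome data are seen settles it.

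**What to change.** In sections 6.10 and 7.2.2, state a fixed sequence. Test 18-month SER change first at two-sided 5%, because the sample size is built on that outcome. Test 18-month AL change at two-sided 5% as confirmatory only if SER is significant; otherwise report AL descriptively. This holds family-wise error at 5% and keeps 46 evaluable per group. In section 7.1, say that the 90% power refers to SER only and that AL power was not calculated. Carry the same wording into the Overview and the section 2 outcome listing.

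The sequence does not supply AL power: the chance of confirming AL becomes the joint power above, which remains unknown.

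A rule that both outcomes must be significant at 5% is an acceptable alternative, provided the power statement is restated for joint success with an explicit AL assumption. An equal split at 0.025 each would also control the error, but it lowers SER power at 46 per group from 90.2% to 84.2%; restoring 90% would need 55 evaluable per group.

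Cost of the fixed sequence: AL cannot be claimed as confirmatory if SER fails. Section 13.2 requires Steering Committee approval and submission to both institutions' review boards before implementation. The sample size does not change.
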